## Abstract

**Background:**

Visual impairment (VI) affects more than 600 million people globally and significantly reduces quality of life. In Singapore, 20% of adults aged 60 years and older (~180,000 people) have VI, a figure expected to double by 2030 due to population aging. While about half of VI cases are due to uncorrected refractive errors, the rest are caused by age-related diseases. The current traditional screening model is a 2-visit, labor-intensive approach with low follow-up rates and frequent unnecessary referrals. Although AI for Disease-related Visual Impairment Screening Using Retinal Imaging, the deep learning model in this study, has demonstrated strong diagnostic performance in retrospective datasets (area under the curve=0.942), key aspects of real-world implementation such as operational efficiency, patient acceptability, workflow feasibility, and cost remain insufficiently studied. As a result, real-world evidence directly comparing artificial intelligence (AI)–assisted and traditional screening pathways is limited.

**Objective:**

This study aims to evaluate the referral accuracy, operational efficiency, acceptability, feasibility, and cost of an AI–assisted screening model compared with the current traditional screening model.

**Methods:**

This study aims to recruit 1000 participants aged 50 years and older using a 2-arm pragmatic randomized controlled trial design. Participants with presenting visual acuity worse than 6/12 (L2) will be randomized 1:1 into either the AI-assisted or traditional screening arms. In the AI-assisted arm, the AI model will analyze retinal photos on-site, with positive cases referred to an optometrist for secondary evaluation. The AI model, previously developed with promising diagnostic accuracy and further validated using community-acquired data, has been integrated with a custom user interface for use in this study. Traditional screening will include pinhole visual acuity, intraocular pressure, slit lamp examination, auto refraction, and retinal photography. All L2 participants will complete a patient-acceptance questionnaire and undergo assessments to determine ground truth.

**Results:**

The study was funded in 2022. Participant recruitment commenced in July 2024, with 487 participants enrolled as of September 14, 2024. Recruitment is ongoing, with study completion anticipated by March 2026 and data analysis expected to begin in April 2026.

**Conclusions:**

This study will provide critical evidence on the clinical utility, feasibility, and cost analysis of AI-assisted VI screening. Our findings may contribute real-world evidence to inform scalable, sustainable screening strategies that enhance efficiency, accuracy, and health system outcomes.

## Introduction

### Background and Rationale

Visual impairment (VI) affects approximately 600 million individuals globally and significantly reduces quality of life, independence, and mobility [1]. In Singapore, one-fifth of adults aged 60 years and older (~180,000 people) experience VI [2]. This figure is expected to nearly double by 2030 due to population aging [1]. Among the VI cases, approximately half result from uncorrected refractive errors, primarily myopia, which can be readily corrected with properly dispensed spectacles available at optical shops. The remaining half are caused by age-related ocular diseases, including cataract, diabetic retinopathy (DR), age-related macular degeneration (AMD), and glaucoma, requiring specialized medical or surgical intervention [3]. Alarmingly, around 70% of older adults with VI in Singapore remain undiagnosed, primarily due to low awareness [4]. Findings from the Singapore Epidemiology of Eye Diseases (SEED) study highlighted that 80% of VI cases among the older adults are treatable [2]. Timely detection through effective vision screening and prompt identification of underlying causes are crucial to prevent disease progression and severe visual loss [5]. Thus, primary prevention and early intervention are essential to mitigate the burden of VI.

The traditional vision screening model commonly used in Singapore involves a 2-visit process. During the first visit, visual acuity (VA) and pinhole tests are conducted, and participants with poor pinhole VA (worse than 6/12) are referred for a second visit on a separate day for additional slit lamp and retinal examinations [6]. While this model provides a structured and thorough screening process, it is relatively manpower-intensive and may require additional effort from participants, potentially impacting follow-up rates and service capacity. As demand for vision screening grows with an aging population, exploring more streamlined and scalable approaches may help enhance accessibility, efficiency, and long-term sustainability.

Artificial intelligence (AI) presents transformative possibilities for health care delivery [7]. Recently, we developed AVIRI (AI for Disease-related Visual Impairment Screening Using Retinal Imaging), a novel deep learning-based algorithm leveraging retinal photography to detect disease-related VI. In a proof-of-concept study published in *Lancet Digital Health* (2021), AVIRI achieved high accuracy (area under the curve [AUC] 0.942) in identifying eye disease-related VI compared with ophthalmologist diagnoses [8]. Although many AI models have shown promising performance on retrospective evaluation, real-world implementation required more than diagnostic accuracy. Successful adoption also depends on workflow feasibility, efficiency, patient acceptability, and cost [9-11]. These aspects of real-world implementations have not been studied in previous AI research. To that end, real-world validation of AI-assisted screening remains limited, with even fewer studies comparing between AI-assisted and traditional screening approaches. To address this gap, we propose an AI-assisted screening model that combines a presenting VA test with AVIRI and will directly compare its performance against traditional screening methods to evaluate efficiency and accuracy in detecting VI.

### Hypothesis and Objectives

This study is designed as a hybrid type 1 effectiveness-implementation trial to evaluate and compare the performance, operational efficiency, acceptability, feasibility, and cost differences between the AI-assisted screening model and the traditional screening model in a community screening setting. A pragmatic randomized controlled trial (pRCT) design will be used to better represent the targeted real-world population. This study will focus on the following specific aims:

Aim 1: To evaluate and compare the referral accuracy between the AI-assisted screening model and traditional screening model for disease-related VI.

Hypothesis 1: The AI-assisted screening model will outperform the traditional screening model in detecting and referring VI cases.

Aim 2: To compare the operational efficiency and acceptability between the AI-assisted screening model and the traditional screening model, and to investigate the feasibility of the AI-assisted screening model.

Hypothesis 2: The AI-assisted screening model will demonstrate greater operational efficiency and acceptability compared to the traditional screening model and will be feasible for implementation in community-based settings.

Aim 3: To compare the overall costs of the AI-assisted screening model and the traditional screening model from a health system perspective.

Hypothesis 3: The AI-assisted screening model will be more cost-effective than the current traditional screening model from a health system perspective.

## Methods

### AI Model Development and Validation

In a proof-of-concept study, AVIRI demonstrated high diagnostic performance, achieving an area under the receiver operating characteristic curve (AUC) of 0.942 (95% CI 0.922‐0.956), with an accuracy of 87.7%, sensitivity of 94.6%, and specificity of 81.3%, compared with the ground truth of ophthalmologists’ clinical diagnoses. External validation using population-based datasets from China, India, and Australia yielded AUCs ranging from 0.859 to 0.935, further supporting AVIRI’s robustness across different populations [8]. While these findings highlight the model’s ability to detect disease-related VI, its real-world performance in community-based settings with undilated eye examinations has not yet been explored.

To address this gap, a previous retrospective evaluation was conducted using 421 retinal images collected in a community setting with the Crystalvue retinal camera (Crystalvue NFC-700; Crystalvue Medical Corporation). This evaluation was part of pilot testing and was not previously published. Multiple domain adaptation strategies were applied to enhance model generalizability, and a ViT-Base architecture, trained on the SEED dataset, was selected as the optimal backbone. This adaptation achieved an AUC of 0.853, specificity of 0.688 (when sensitivity fixed at 80%), and *F*_1_ score of 0.347. Additionally, a user interface was developed to facilitate clinical integration, allowing researchers to input clinical data and generate automated diagnostic reports using AVIRI. These findings provide the foundation for further prospective validation, evaluating AVIRI’s real-world performance in an AI-assisted vision screening model.

### Sample Size Calculation

This study will recruit a total of 1000 participants aged 50 years and older using a 2-arm pRCT design with broad inclusion criteria based solely on age. Of these, 500 participants are targeted to have presenting VA better than 6/12 (L1), a number determined based on operational feasibility in community screenings.

Participants with presenting VA worse than 6/12 (L2) will be randomized to either the AI-assisted or traditional screening model. Sample size estimation for this randomized comparison was based on an assumed accuracy of 70% for the current traditional screening model and prevalence of 18% for any VI, 11% for disease-related VI, and 8% for refractive-error related VI (prevalence estimates were based on the SEED study) [2]. Detecting a clinically meaningful difference of 10% between the 2 screening models with 80% statistical power at a 5% 2-sided type I error requires 250 participants per arm. Therefore, a total of 500 randomized participants (L2) will be included in the primary analysis.

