### Randomization

VI is defined according to the United States VI definition as having a presenting VA worse than 20/40 (equivalent to 6/12) in the better-seeing eye [3]. Participants with presenting VA of 6/12 or better (L1) will not be randomized. These participants will receive a basic ocular assessment, including fundus photography and anterior eye imaging. The collected images will not be used in the comparative analysis between the AI-assisted and traditional screening arms.

Participants with presenting VA worse than 6/12 (L2) will be randomized into either the AI-assisted screening arm or the traditional screening arm using a 1:1 allocation ratio. Randomization will be conducted at the patient level, ensuring that both eyes of the same participant are assigned to the same study arm. The randomization sequence will be generated by an independent statistician using the “randomizeR” package in R statistical software. This approach ensures an unbiased allocation process while maintaining the integrity of the study design.

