### Data Analysis Plan

#### Model Performance

The AI model was based on the ViT-base backbone, which was initialized using pretrained weights obtained through supervised learning on the ImageNet-21k dataset [20]. Fine-tuning was carried out for 40 epochs to allow for sufficient learning while reducing the risk of overfitting. The process was performed using a batch size of 16, with a fixed learning rate of 1 × 10⁻⁵, weight decay set at 5 × 10⁻⁴, and the default drop path rate applied. To evaluate the effectiveness of the AI-assisted screening model compared to the traditional screening model in detecting VI, both models will be assessed against the ground truth. Overall accuracy, sensitivity, and specificity will be calculated and compared using *z* tests for 2 proportions. Additionally, AUC and the area under the precision-recall curve will be determined for each model. Differences in AUC and area under the precision-recall curve between the two models will be analyzed using bootstrap resampling. All quantitative analyses for model performance will be conducted using R, including diagnostic accuracy metrics and comparative statistical tests.

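### The stated 250 per arm does not give 80% power for 70% versus 80% accuracy at two-sided 5%; those inputs need about 294 per arm, and 250 gives about 73% power

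*Protocol article*

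**What the plan says.** All inputs to the calculation are in the protocol article.

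- **Baseline** (Sample Size Calculation): "assumed accuracy of 70% for the current traditional screening model".
- **Effect** (same section): a "clinically meaningful difference of 10% between the 2 screening models". Hypothesis 1 under Hypothesis and Objectives gives the direction: "The AI-assisted screening model will outperform the traditional screening model in detecting and referring VI cases".
- **Result** (same section): "80% statistical power at a 5% 2-sided type I error requires 250 participants per arm", and hence "a total of 500 randomized participants (L2) will be included in the primary analysis".
- **Design** (Randomization): "Randomization will be conducted at the patient level", "using a 1:1 allocation ratio".
- **Endpoint** (Primary Outcomes): the proportion of participants whose referral decision agrees with the reference panel, which is a binary outcome.
- **Test** (Model Performance): "Overall accuracy, sensitivity, and specificity will be calculated and compared using" z tests for two proportions.

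The sample size section also lists prevalences of 18% for any visual impairment, 11% for disease-related impairment and 8% for refractive-error impairment. It gives no other accuracy assumption, no one-sided test and no continuity correction.

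**The concern.** The section states the per-arm size as what its own inputs require, so a reader should be able to recover it with the standard formula. The usual result for 70% versus 80% at two-sided 5% and 80% power is just under 300 per arm, and 250 is clearly lower.

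At stake is the power statement for the primary comparison. If it is overstated, a non-significant accuracy result could be taken as stronger evidence against a 10-point gain than the trial can give. The trial would also be reported as having a type II error that it does not have.

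**Working it through.** **Inputs.** p1 = 0.70 and difference 0.10 (Sample Size Calculation); p2 = 0.80, because Hypothesis 1 expects the AI-assisted arm to be better; two-sided 5%, so z = 1.960; 80% power, so z = 0.8416; independent arms, 1:1 (Randomization); z test for two proportions (Model Performance).

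**Step 1. Try to reproduce 250 with the stated inputs.** With pooled variance under the null, the mean proportion is 0.75 and

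n = [1.960 × √(2 × 0.75 × 0.25) + 0.8416 × √(0.70 × 0.30 + 0.80 × 0.20)]² / 0.10²
= [1.960 × √0.375 + 0.8416 × √0.37]² / 0.01
= (1.2002 + 0.5119)² / 0.01 = 293.2, so **294 per arm** (588 in total).

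The stated figure is not reproduced. The shortfall is 294 − 250 = 44 per arm, or 88 in total.

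**Step 2. Other two-sided formulas, same inputs.**

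| Formula | n per arm |
|---|---|
| Unpooled variance: (1.960 + 0.8416)² × 0.37 / 0.01 | 290.4, so 291 |
| Arcsine | 291.7, so 292 |
| Pooled | 293.2, so 294 |
| Pooled with continuity correction | 312.8, so 313 |

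None gives 250.

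**Step 3. Other readings of the 10%, two-sided, pooled.** A relative gain (70% versus 77%) needs 623 per arm. A 10-point fall (70% versus 60%) needs 356. Both move further from 250.

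**Step 4. Power at 250 per arm, 70% versus 80%.**

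Power = Φ{[0.10 − 1.960 × √(0.375/250)] / √(0.37/250)}
= Φ{(0.10 − 0.0759) / 0.03847} = Φ(0.626) = **73.4%**.

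The unpooled version gives 73.9% and the arcsine version 73.7%. Exact binomial enumeration of the pooled z test gives 73.7%, and a continuity-corrected test 69.9%.

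**Step 5. What 250 per arm does detect.** Solving the same power expression for the difference above 70% that gives 80% power yields 0.1077, or about **10.8 points**.

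**Step 6. Which calculations come near 250.**

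| Calculation | n per arm before rounding up | Agrees with the text? |
|---|---|---|
| 75% versus 85%, two-sided, pooled: (1.1087 + 0.4724)² / 0.01 | 249.98 | No, the baseline is stated as 70% |
| 70% versus 80%, one-sided 5%, continuity-corrected | 250.4 | No, the test is stated as two-sided |
| 70% versus 80%, two-sided, variance taken as 2 × 0.80 × 0.20 | 251.2 | No, it ignores the 70% arm's variance |

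Each needs an input or formula at odds with what is written.

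**Step 7. Prevalences.** The formula uses only the two accuracies, the error rates and the allocation ratio. Everyone randomised already has presenting acuity worse than 6/12. The 18%, 11% and 8% therefore do not enter and cannot account for the gap.

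**The case against.** The best case for the plan is that the gap is modest. Power falls by 80 − 73.4 = 6.6 percentage points, and the detectable difference moves from 10.0 to 10.8 points. The 70% is itself an assumption, and the confidence interval at the end will show the precision achieved whatever was planned. All of this is true. It is why the remedy is a change of wording at the same sample size and not a redesign. It does not make the sentence correct: the section claims that these inputs require 250, and they do not.

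A reader might go further than the document allows in three ways.

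- **That 250 arose because 75% versus 85% was used.** The match at 249.98 is striking, but neither 75% nor 85% appears anywhere as an accuracy assumption. The one-sided continuity-corrected route at 250.4 is practically as close. The origin is unknown.
- **That exclusions will lower the power further.** The article describes a single visit. Poor images are retaken and then logged, and cases without a majority go to consensus and then to a senior adjudicator. It states no exclusion from the primary analysis, so a specific loss rate would be invented.
- **That power against a 10-point fall is the relevant figure.** Hypothesis 1 expects the AI-assisted model to do better, so 70% versus 60% is not the planned alternative.

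**Conclusion.** The power statement is wrong as written. On the section's own inputs the requirement is about 294 per arm (291 to 313 across two-sided formulas), and 250 per arm gives about 73% power, a type II error of about 27%. This rests on three readings: the 10% is an absolute gain over 70%, the arms are independent with 250 analysed in each, and the test is the two-sided z test that the article names. No other two-sided reading of the stated inputs recovers 250. How the number came about cannot be settled from the document, and the finding does not depend on it.

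**What to change.** Keep 500 randomised participants and replace the power sentence in Sample Size Calculation with wording such as: *With 250 participants per arm and a two-sided 5% test, the trial has about 73% power to detect 80% versus 70% accuracy, or 80% power to detect a difference of about 10.8 points from 70%.* State also that the prevalences are background and are not inputs to this calculation, or move them elsewhere.

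Change the 70% baseline only if the sponsor's records show that another value was actually used. It should not be altered afterwards to suit the sample size, particularly as the Results section reports recruitment under way.

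The cost is a sentence or two and no extra participants. The stated power becomes less favourable. The Results section places the statistical analysis from April 2026, and the correction should be made before it begins.

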### Randomization

VI is defined according to the United States VI definition as having a presenting VA worse than 20/40 (equivalent to 6/12) in the better-seeing eye [3]. Participants with presenting VA of 6/12 or better (L1) will not be randomized. These participants will receive a basic ocular assessment, including fundus photography and anterior eye imaging. The collected images will not be used in the comparative analysis between the AI-assisted and traditional screening arms.

Participants with presenting VA worse than 6/12 (L2) will be randomized into either the AI-assisted screening arm or the traditional screening arm using a 1:1 allocation ratio. Randomization will be conducted at the patient level, ensuring that both eyes of the same participant are assigned to the same study arm. The randomization sequence will be generated by an independent statistician using the “randomizeR” package in R statistical software. This approach ensures an unbiased allocation process while maintaining the integrity of the study design.

### Study Setting

This study will be conducted at Pioneer Polyclinic, a public primary care clinic located in the western region of Singapore. Polyclinics in Singapore are government-funded health care institutions that provide subsidized outpatient medical services, including acute care, chronic disease management, health screenings, and preventive care. They serve as a key component of the country’s primary health care network and are typically staffed by physicians, nurses, and allied health professionals.

Pioneer Polyclinic is part of the National University Polyclinics (NUP) group under the National University Health System. It serves a multiethnic residential population comprising predominantly older adults and middle-aged individuals, with a substantial proportion managing chronic conditions such as hypertension, diabetes, and hyperlipidemia. The clinic is located in a mature public housing estate, where access to subsidized screening and community-based care is particularly important.

### Data Collection

#### Study Workflow

##### Recruitment and Study Procedures

Recruitment will take place at Pioneer Polyclinic (National University Polyclinics) over an 18-month period. Each participant will attend a single study visit, which is expected to last approximately 30 to 90 minutes. Participants will be recruited through 3 main channels: (1) review of past study records to identify eligible individuals, (2) word-of-mouth referrals, and (3) display of an electronic brochure (e-brochure) on screens within participating polyclinics. For the first recruitment channel, only individuals who meet the study’s eligibility criteria will be invited to participate. Eligible participants must have complete clinical data and retinal imaging records. They must also have previously provided consent to be recontacted.

Both the AI and traditional screening arms will use the same fundus cameras (Crystalvue) and will follow identical equipment calibration protocols according to manufacturer recommendations. All image acquisition will be performed by trained clinical research coordinators who have completed standardized certification in retinal imaging. Refresher training and inter-operator assessments will be conducted prior to and throughout the study to minimize variability.

##### Control Arm

Participants will first sign informed consent before proceeding with any assessment. After being randomized into the traditional model arm, the screening will follow the standard examination workflow used in the traditional screening model, which consists of pinhole VA, intraocular pressure, auto refraction, slit lamp examination, and retinal photography. The fundus photographs will be reviewed by the onsite optometrists, and any images of insufficient quality will be retaken immediately to improve clarity. If image quality remains inadequate, the participant’s ID will be flagged in the study log. Referral decisions will be made by the onsite optometrists, incorporating the findings from all other screening tests. After receiving the referral outcome, participants will be invited to complete a patient-acceptance questionnaire to assess their perceptions and satisfaction with the traditional screening model (Multimedia Appendix 1). Finally, anterior eye photography and subjective refraction will be performed to establish the ground truth status for the referral decision (Figure 1).

